**Figure 1 figure1:**
[figure not shown]
Schematic diagram of study plan.

### Study Setting

Participants will be screened and enrolled at the NARIP in Cheruthuruthy, Thrissur, an institute under the Central Council for Research in Ayurvedic Sciences, Ministry of Ayush, government of India. The institute is well equipped for comprehensive Ayurvedic assessments and interventions, ensuring a high standard of participant care and protocol adherence during the *nasya karma* procedure. fMRI assessments will be carried out at AIMS, which is equipped with state-of-the-art imaging technology and experienced radiologists, providing the advanced neuroimaging capabilities necessary for detailed BOLD fMRI studies.

### Sample Size

As this is designed as an exploratory study aiming to gather preliminary data on the neurophysiological effects of the *nasya karma* procedure and its impact on various health parameters, a sample size of 60 (30 per group) is considered appropriate to achieve the study objectives and provide valuable insights that will inform the design of future, larger-scale clinical trials. Feasibility is a critical consideration as recruiting a larger sample of participants willing to undergo both the *nasya karma* procedure and twice-repeated fMRI assessments may be challenging, particularly among healthy volunteers. However, the expected variation in response to the interventions is likely to be lower than that in a patient population, which will allow for meaningful conclusions to be drawn from a smaller sample size. Similarly, a sample size of 60 balances the need for preliminary data with the practical constraints of the logistical and financial resources of the study.

### Randomization and Allocation

Eligible participants in this study will undergo random allocation to either the intervention or control group using a computer-generated random sequence prepared by an independent statistician, ensuring an unbiased approach to treatment assignment. Each random sequence number will be securely sealed in opaque envelopes, with the enrollment ID on the outside. Before enrollment, participants will open these envelopes to determine their allocated group to minimize bias.

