## Methods

### Ethical Considerations

The study will strictly adhere to the principles outlined in the Declaration of Helsinki (World Medical Association; 2013). Before enrollment in this trial, all participants will be required to provide informed consent by signing a consent form. The protocol has undergone rigorous ethical review and received approval from the institutional ethics committee of the National Ayurveda Research Institute for Panchakarma (NARIP), Cheruthuruthy, Thrissur, Kerala, Peripheral Institute of CCRAS, Ministry of Ayush, Government of India and Scientific Review Board, Amrita Institute of Medical Sciences, Kochi (F.No.8/16/2023/NARIP/Tech meeting/2508 dated March 31, 2023), and the study is registered with the Clinical Trials Registry – India. The participants will be given incidental support charges of INR 100 (US $1.11) per visit as participant compensation. The trial is covered by clinical trial insurance for any incidents, and the participants will receive appropriate compensation if these arise.

Protocol amendments, if any are needed in the course of the trial, will be communicated to the institutional ethics committees at Amrita Institute of Medical Sciences, Kochi, and NARIP, Cheruthuruthy, India. Personal information about potential and enrolled participants will be collected, shared, and maintained in a confidential manner before, during, and after the trial unless subjected to judiciary (ie, court-related) disputes. Access to trial data will be granted only to the research team involved at NARIP and the Amrita Institute of Medical Sciences (AIMS). There will be no public access to the trial dataset. Dissemination policy includes publication of study findings in peer-reviewed indexed international journals.

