This study is structured as an exploratory randomized controlled clinical trial, with participants allocated in a 1:1 ratio to the intervention and control groups, matched for age and sex to comprehensively assess and evaluate the neurophysiological and holistic health effects of the *marsha nasya karma* procedure in comparison to a control group (Figure 1). Settings of the study include NARIP and AIMS.

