### Secondary Outcome Measures

These include the therapeutic effects of *marsha nasya karma* on cognitive function assessed via the Montreal Cognitive Assessment scale [11], perceived stress assessed using the Perceived Stress Scale [12], anxiety assessed using the Hamilton Anxiety Rating Scale [13], and health-related quality of life assessed using the 36-Item Short Form Health Survey [14]. The secondary outcomes will be assessed before the intervention and on the 1st and 30th days following the *nasya karma* therapy.

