#### Blinding

In this study, participant blinding is not feasible as the intervention involves a procedural administration (*nasya karma*) where participants are aware of undergoing the procedure and the study primarily aims to evaluate the procedural effect rather than an isolated pharmacological effect. Assessor blinding will also not be implemented as the primary outcome measure is fMRI, an objective instrumental assessment that is not subject to assessor interpretation bias during data acquisition.

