#### Protocol Adherence Monitoring

In this study, all *nasya karma* procedures will be administered at the NARIP by trained investigators on alternate days. Participants will not perform *nasya karma* at home. This approach ensures direct procedural supervision, standardized administration, and immediate monitoring for any adverse effects or participant discomfort. Direct assessment by the investigator at each session enhances protocol adherence, fidelity, and the overall robustness of study execution, eliminating the variability associated with home-based administration and, thereby, strengthening the internal validity and reliability of the study findings as in Table 1.

**Table 1 table1:** Gantt chart.

		Week 0	Baseline		Intervention period (1st-13th day)	Follow-up	
			1st day	1st day (immediately after *nasya*)		14th day	30th day
Participant screening, including laboratory tests		✓					
Informed consent		✓					
Randomization		✓					
Intervention: *nasya karma* (group A)			✓		✓		
Control (group B): without *nasya karma*							

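### Participants learn their arm before enrolment and before the day-1 baseline scan, and the reason for waiving assessor blinding covers image acquisition only

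*Protocol article*

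**What the plan says.** - **Allocation.** Randomization and Allocation describes a "computer-generated random sequence prepared by an independent statistician". It continues: "Each random sequence number will be securely sealed in opaque envelopes, with the enrollment ID on the outside". It then says: "Before enrollment, participants will open these envelopes to determine their allocated group to minimize bias".
- **Consent.** Ethical Considerations says: "Before enrollment in this trial, all participants will be required to provide informed consent by signing a consent form". The text does not order consent against the opening of the envelope. Table 1 lists consent above randomization, both in Week 0.
- **Timing of baseline.** Table 1 ticks the row "Randomization" in Week 0 and the first fMRI on day 1, for both groups. For the clinical scales the abstract gives days 1 and 30. Secondary Outcome Measures gives a time before the intervention plus days 1 and 30. Table 1 ticks day 30 only.
- **Matching.** The design paragraph under Interventions says participants are "allocated in a 1:1 ratio to the intervention and control groups, matched for age and sex". The allocation section mentions neither factor.
- **Blinding.** Participants are not blinded. Assessor blinding is also waived, because fMRI is "an objective instrumental assessment that is not subject to assessor interpretation bias during data acquisition".
- **Outcomes outside that reason.** Secondary outcomes include "anxiety assessed using the Hamilton Anxiety Rating Scale" and the Montreal Cognitive Assessment, as well as self-reported stress and quality of life.

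**The concern.** Sealed envelopes protect a trial only until they are opened. After that, the person must already be committed and counted. Here disclosure comes before enrolment, and the plan presents this as a safeguard. Someone who sees no intervention, or who sees repeated nasal instillation, can leave without ever being enrolled. If those who leave differ from those who stay, the two groups of 30 are no longer the groups that were randomized.

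The research hypothesis is a change from baseline, and the baseline scan is made when participants already know what they will receive. Anticipation can therefore be part of the baseline itself.

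Participant blinding is conceded as infeasible. Blinded scale raters and a blinded image analysis are then the main protections left. The plan waives assessor blinding for the whole trial on a ground that fits only the scanner's output.

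**Working it through.** No figure in the plan is at stake, so the check is mainly one of order and scope.

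**1. Order of steps.**
- Week 0: screening and laboratory tests, consent, randomization (Table 1). The envelope is opened before enrolment (Randomization and Allocation).
- Day 1: baseline fMRI in both groups, then the first procedure and a second scan in the intervention group only.
- Day 14: fMRI in both groups. Day 30: clinical assessment.

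Read together, the arm is known before enrolment and before the baseline scan. For the scales, the day of the baseline measurement is not fixed consistently, so the same can be said of them only if day 1 is meant.

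**2. Scope of the blinding reason.** The stated reason concerns data acquisition. Three activities lie outside it:
- scoring of the Hamilton and Montreal scales;
- the decision to repeat mapping after head movement (Resting Phase fMRI);
- image processing and inference. fMRI Data Analysis leaves preprocessing to either of two toolboxes and sets voxel P<.01 with cluster-level FDR at P<.05. Multiple-Comparison Correction sets voxel P<.001 uncorrected with cluster-level FWE at P<.05. An analyst who knows the arms could choose among these after seeing results.

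**3. Matching.** One section says the groups are matched for age and sex. The section that describes the sequence gives no mechanism for it. The group comparisons under Statistical Analysis, Overview are unadjusted t or Mann-Whitney tests. Age and sex are controlled only in the correlations between clinical and fMRI measures.

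**4. Scale under assumed values.** The documents give no bias size, so these are illustrations only.
- *False-positive rate under a pure bias of b SD.* Inputs from the plan: 30 per group, two-sided 0.05. Two-sample t test, df = 30 + 30 − 2 = 58, noncentrality = b × √(30/2) = b × √15.

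| Assumed bias b (SD) | 0 | 0.1 | 0.2 | 0.3 | 0.4 | 0.5 |
|---|---|---|---|---|---|---|
| False-positive rate | 5% | 6.7% | 11.9% | 20.8% | 33.2% | 47.8% |

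- *Loss after opening, worst case.* If a share f of one arm, all with the lowest values, leaves, the mean of that arm moves by φ(z_f)/(1 − f) SD, where z_f is the normal quantile of f. For f = 5%, 10% and 20% this is 0.11, 0.20 and 0.35 SD. Real refusals would be less extreme.

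**The case against.** The case for the plan has weight on several points.

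- **Concealment up to opening is sound.** The sequence comes from an independent statistician and the envelopes are sealed and opaque. Nobody can foresee the next allocation. The risk is limited to what happens after opening, and it shrinks if consent comes first, as the order of rows in Table 1 suggests, and if everyone randomized is counted.
- **Screening comes first.** A reader might infer that nothing at all is measured before allocation. That is not supported: those randomized are eligible people, and screening tests are in Week 0. The point holds for the baseline fMRI, and for the scales only as far as their day can be read.
- **The image analyst is never mentioned.** A reader might infer that the analyst is known to be unblinded. The documents do not say so, and coded files may be specified in a fuller plan. What stands is that the one reason given for waiving blinding does not cover analysis, and that the choices left open make masking worthwhile.
- **Other stronger readings fail.** The documents do not say when enrolment IDs are issued, so pre-numbered envelopes would fit the text. They do not say the sequence is unstratified, so matching may be shorthand for stratification. The modified intention-to-treat set is undefined here and may be defined elsewhere, so it cannot be said to hide refusals. Chance imbalance in sex under a simple sequence is not a measure of selection or expectation bias.
- **Limits of any repair.** Expectation after baseline remains in an open comparison with no intervention, and blinded raters do nothing for self-reports. The immediate post-procedure scan exists only in the intervention group, so coding cannot mask it.
- **The trial is exploratory and the scales are secondary.** That lowers the stakes of the scale ratings. It does not excuse an avoidable bias in data meant to inform larger trials.

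**Conclusion.** The point holds in a limited form. The order of opening and enrolment is a stated rule, not a detail left to another document. Followed as written, it permits selective non-enrolment once the arm is known and places the baseline scan after disclosure. The waiver of assessor blinding rests on a reason narrower than the waiver. Bias can enter by these routes. The documents do not show that it will, nor in which direction.

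Its size cannot be derived from the document. The rates and shifts in the working depend on assumed biases and on worst-case departures. They show only that, with 30 per group, a modest bias is enough to matter. The conclusion on the baseline scan rests on Table 1 being followed. The conclusion on selection rests on the word enrolment being used in its ordinary sense.

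**What to change.** 1. **Opening.** Open the envelope only after consent, confirmed eligibility and enrolment. Where logistics across the two sites allow, do so after the day-1 baseline scan and scales. State one day for the baseline scales and tick it in Table 1.
2. **Counting.** Treat everyone whose envelope is opened as randomized, and report refusals after opening by arm.
3. **Blinding statement.** Limit the present justification to image acquisition.
4. **Image analysis.** For the between-group contrast of day-1 baseline and day 14, give the analyst arm-coded files, and fix one pipeline and one set of thresholds before the codes are broken. Keep the intervention group's extra day-1 scan out of that file set until the contrast is final, since a third session reveals the arm. State that the immediate-response analysis cannot be masked.
5. **Scales.** Where existing staff permit, have people who do not give the procedure score the Hamilton and Montreal scales.
6. **Matching.** Either stratify the sequence by sex and age band and say so, or delete the claim of matching and adjust the group comparisons for both.

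**Cost.** No extra participants or scans. Items 2, 3, 4 and 6 are wording, file coding and an analysis decision. Item 1 has a real cost if opening follows the baseline scan: allocation moves from the enrolling institute to the imaging centre on scan day, and a procedure slot must be held for every participant. Item 5 depends on staff the documents do not describe. If enrolment has already finished, the coded analysis, the fixed pipeline, adjustment for age and sex, and reporting of refusals after opening remain possible.

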**Methods:**

A total of 60 healthy volunteers in the age group of 20 to 40 years who fulfill the selection criteria will be recruited for this randomized controlled trial at the National Ayurveda Institute for Panchakarma, Cheruthuruthy, Kerala, India, and randomized in a 1:1 ratio to either the intervention group (n=30; group 1, receiving *nasya karma* with *anu taila*, an oil-based formulation manufactured using a paste and decoction of herbal medicines with oils as the base material, for a period of 14 days) or the control group (n=30; group 2, not receiving any intervention). The participants will undergo task-based and resting fMRI on day 1 (twice on day 1 before administration and 15 minutes after *nasya karma* for participants in group 1) and day 14 to map the neurophysiological response to *nasya karma* of the brain. A comprehensive neuroimaging protocol using structural magnetic resonance imaging and fMRI will be used in the study. The effect of *nasya karma* on sleep, psychological well-being, cognition, and quality of life will be assessed on the 1st and 30th days in both groups.

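### Participants open the allocation envelope before they are enrolled, so entry can depend on the known arm, and the day-1 fMRI baseline is recorded with allocation known

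*Protocol article*

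**What the plan says.** All references are to the protocol article.

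- **Randomization and Allocation.** An independent statistician prepares a computer-generated sequence. "Eligible participants in this study will undergo random allocation to either the intervention or control group", so screening comes first. "Each random sequence number will be securely sealed in opaque envelopes, with the enrollment ID on the outside". Then: "Before enrollment, participants will open these envelopes to determine their allocated group to minimize bias".
- **Ethical Considerations.** "Before enrollment in this trial, all participants will be required to provide informed consent by signing a consent form". Consent and envelope opening are thus both placed before enrollment, and their order relative to each other is not stated here.
- **Table 1.** Screening, informed consent and the row "Randomization" are all ticked at Week 0. The first scan of both groups is in the later baseline column, day 1.
- **Abstract, Methods.** "The participants will undergo task-based and resting fMRI on day 1". The sleep, well-being, cognition and quality-of-life measures "will be assessed on the 1st and 30th days in both groups".
- **Secondary Outcome Measures.** The scales are taken before the intervention and on days 1 and 30 following therapy. Table 1 ticks clinical assessment on day 30 only.
- **Blinding.** Neither participants nor assessors are blinded.
- **Statistical Analysis, Overview.** Analysis follows a modified intention-to-treat principle in the full analysis set. The article does not define that set.

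**The concern.** Concealment has to hold until a person is irrevocably in the trial. Here it ends one step too early: the candidate learns the arm and is enrolled afterwards.

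The two arms ask for very different things. One involves repeated nasal procedures and three scans; the other involves two scans and no treatment. The Sample Size section itself expects difficulty in finding healthy volunteers willing to have both the procedure and repeated scanning. A preference in either direction is therefore plausible. If people act on it before enrollment, the enrolled arms are no longer comparable by design, and analysis cannot fully repair that.

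The second issue is the baseline. Participants who know that a nasal procedure follows may enter the scanner in a different state from those who know that nothing follows. Resting-state signal and task performance could respond to that, and so could self-reported stress and anxiety. Any such shift passes into the change from baseline.

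**Working it through.** **Step 1: order of events.** The plan gives no figure on this point, so the check starts by putting the statements in sequence.

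| Event | When | Source |
|---|---|---|
| Screening, consent | Week 0 | Table 1 |
| Randomization | Week 0 | Table 1 |
| Envelope opened by the participant | Before enrollment | Randomization and Allocation |
| Enrollment | After opening | Follows from the line above |
| First fMRI, both arms | Day 1 | Abstract; Table 1 |
| First scales | Day 1, or before the intervention, or not ticked | Abstract; Secondary Outcome Measures; Table 1 |
| First procedure, intervention arm | Day 1, after the first scan | Abstract; Table 1 |

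The first problem, opening before enrollment, is stated outright. The second, an fMRI baseline taken with allocation known, follows from Table 1 alone and does not depend on how the word enrollment is read. For the scales, the three statements conflict and the order cannot be settled.

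**Step 2: possible size of selection (assumed inputs).** Let a share p of those who draw one arm decline, and let decliners differ from acceptors by δ SD. The enrolled mean of that arm then differs from the mean of all who drew it by p × δ. The article gives neither p nor δ; I take p = 0.1 to 0.3 and δ = 0.5 to 1.0, with no declining in the other arm. The false-positive rate is for one two-sided t test at .05 with 30 per arm and no true effect (58 df, noncentrality = shift × √(30/2) = 3.873 × shift).

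| p | δ | Shift (SD) | False-positive rate |
|---|---|---|---|
| 0.1 | 0.5 | 0.05 | 5.4% |
| 0.1 | 1.0 | 0.10 | 6.7% |
| 0.2 | 0.5 | 0.10 | 6.7% |
| 0.2 | 1.0 | 0.20 | 11.9% |
| 0.3 | 0.5 | 0.15 | 8.8% |
| 0.3 | 1.0 | 0.30 | 20.8% |

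As a yardstick, the Power Analysis section plans on d = 0.6, so the shifts are 0.05/0.6 = 8% to 0.30/0.6 = 50% of that.

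**Step 3: change scores.** The selection figures do not carry over directly. If decliners differ by a stable amount, that amount is in both the baseline and the follow-up and cancels in the difference.

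An anticipation shift at baseline behaves differently because it enters the change. With equal variances and correlation r between occasions, the SD of the change is √(2(1 − r)) raw SDs. A 0.30 SD baseline shift is then 0.30/√(2(1 − r)) change-score SDs: 0.24 at r = 0.2, 0.30 at r = 0.5 and 0.47 at r = 0.8. The article gives no r.

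**Step 4: which comparison is exposed.** The primary outcome has an immediate and a 14-day component. Table 1 gives controls no second scan on day 1, so the immediate component has no between-arm pre/post contrast for selection to bias; only anticipation can act on it. The 14-day comparison between arms is exposed to both.

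**The case against.** **The wording may be loose.** An envelope carrying an ID, "with the enrollment ID on the outside", suggests that a number exists before opening, and Table 1 lists consent above randomization. On that reading the person is already screened, consented and numbered, and a refusal is a withdrawal after randomization. This is a fair reading, but no section says that consent comes before opening, and the sentence as written says the opposite about enrollment. Table 1 still puts randomization ahead of the day-1 scan.

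**The envelopes still do something.** A reader might infer that concealment fails altogether. It does not: the independent sequence and the opaque envelopes hide the next assignment from recruiting staff until opening. What remains is self-selection by the participant afterwards, which the sequence permits but which the article does not say will occur.

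**Refusals might be counted.** A reader might infer that decliners are certain to vanish from the analysis. The article names a modified intention-to-treat principle without defining it, and the definition may stand in the full protocol or analysis plan. They may go uncounted; that is as far as the text goes.

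**The larger error rates do not transfer.** The 20.8% is the extreme corner of assumed values, for a single t test on a raw outcome. The imaging analyses use voxel thresholds with cluster-level correction, so the figure says nothing direct about them. This objection stands.

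**The trial is open-label and exploratory.** True, but that makes comparability through randomization more important, because no blinding offsets its loss.

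**Conclusion.** The point holds. A stated procedure lets entry depend on the known arm, and the schedule has the primary-outcome baseline recorded after allocation is revealed. This is a wrong order of steps, not detail left to another document, and it should be corrected.

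The amount of bias is unknown. Under the assumed decline rates and decliner differences, the between-arm shift on a raw outcome is 0.05-0.30 SD. It would be smaller for change scores to the extent that the difference between decliners and acceptors is stable.

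The documents do not support saying that every baseline is taken with allocation known. That is firm for fMRI and unresolved for the scales. Nor do they support saying that lost comparability biases both components of the primary outcome, since the immediate one has no control-arm counterpart.

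**What to change.** 1. Reword Randomization and Allocation, and match Table 1 to it, so that the envelope is opened only after signed consent, confirmed eligibility and enrollment. Drop the claim that opening before enrollment reduces bias.
2. Log the date and time of each opening and count everyone whose envelope is opened as randomized. If envelopes have already been opened, report by arm how many were opened and how many of those people were not enrolled.
3. Where the day-1 flow allows, open the envelope after the baseline scales and baseline scan and before the first procedure. This needs two reconciliations. The Interventions section places assessment-day procedures at the scanning hospital, whereas Protocol Adherence Monitoring places all of them at the Ayurveda institute. The Abstract, Secondary Outcome Measures and Table 1 must also agree on when the scales are first taken.

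Items 1 and 2 cost wording and a log, with no added visit or participant. Item 3 has a small price: the day-1 procedure slot is confirmed only on the day, and some slots will be held for people who draw control. If opening takes place at the scanning hospital, the envelopes and log must be available there.
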